### Child recruitment

Children born in 2021 or later will be recruited from two sources: (1) households listed in the C-RCT baseline and (2) children currently enrolled in selected daycares. We recruit C-RCT baseline households following the midline survey, after enumerator trust has been built. For the daycare user sample, we ask providers to send study information and consent forms home with parents, and we send enumerators to directly recruit during drop-off times. See detailed recruitment procedures in online supplementalappendix A.1.

### Data collection

Enumerators will conduct assessments with these two samples of children, measuring height and weight for all children aged 0–5 to measure stunting and wasting and applying the IDELA for children aged 3 and older.^20^ These assessments will be carried out at local daycares (with agreement from daycare owners) and community centres. Measurements of height and weight will follow the 2019 WHO/UNICEF guidelines,^21^ and IDELA will be implemented following the tool guidelines. Details are provided in online supplemental appendix A.1.4 and A.1.5, respectively.

Data collection will be done in two stages, one in October 2025 and one in January 2026. (The two-stage split is because schools in Kenya are generally closed from November to January). Each stage of data collection will be done over 2 days in each community, with two enumerators per day.

All instruments will be programmed into SurveyCTO and administered using tablets. Enumerators will carry manipulatives and other materials as necessary.

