**Trial registration number:**

AEARCTR-0011747.

STRENGTHS AND LIMITATIONS OF THIS STUDYWe use well-established methods and tools to measure nutritional status and early child development: we conduct direct anthropometric assessments using standardised field protocols, and we measure early child development outcomes using a validated, age-appropriate instrument (International Development and Early Learning Assessment) administered by trained enumerators.Data collection targets children aged 0–5 living in informal settlements across Kenya, a hard-to-reach population at high nutritional risk.Randomised assignment to differing levels of exposure to high-quality daycare provides a rigorous design to compare child outcomes while minimising confounding from provider and household characteristics.The sample is not randomly drawn from the informal settlements, and the sample of daycare users could not be recruited prior to randomisation due to high turnover in daycare enrolment.Due to the nature of the setting where measurements need to take place, collected data may be noisier, as some children who are being weighed may not be minimally dressed and the child development assessment may be conducted in a more crowded or distracting area than ideal.

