### Data analysis

First, we will analyse and produce descriptive statistics of the key child development outcomes listed above. Second, we will compare these measurements for children in the treatment communities to those in control communities according to the larger study’s randomised design using multivariable regression. We will include controls for child age, sex and strata (county) fixed effects.

We will also examine these outcomes separately for the C-RCT baseline sample and daycare user sample. Because C-RCT baseline households were identified prior to randomisation and the intervention, we anticipate that differences in outcomes will reflect the causal intention-to-treat impact of improved childcare in the community. For the daycare user sample, we will capture the treatment-on-treated effect, but this could be biased if the quality improvement affected the selection of children into daycares.

We will restrict our child development analysis to children for whom we obtain IDELA data. Furthermore, we restrict our nutritional status analysis to children for whom we obtain valid anthropometric measurements. In the event of missing independent variables, we will code them as zero and include a missing variable flag.

Cross-sectional data gathered concurrently through caregiver and daycare firm surveys will produce a large dataset for measuring the relationship between early child development and nutritional status, as well as whether paid caregiving arrangements are associated with children’s health and development outcomes.

The final report of this study will follow the general CONSORT.

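### The daycare-user sample is defined by current enrolment with no record of enrolment start, so its treatment-on-treated estimate averages over unknown and possibly very short exposure

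*Protocol article*

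**What the plan says.** All references are to the protocol article.

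- **Who enters.** Under Child recruitment, the second source of children is "children currently enrolled in selected daycares". The section ties eligibility to birth year and current enrolment, not to when the child joined. It refers to appendix A.1 (not shown) for detailed procedures.
- **Turnover.** The strengths and limitations box says that "the sample of daycare users could not be recruited prior to randomisation due to high turnover in daycare enrolment".
- **What is recorded.** Under Child age data, the form that daycare parents return with their consent is described as asking date of birth. Enrolment start date is not mentioned.
- **Timing.** Under Data collection: "Data collection will be done in two stages, one in October 2025 and one in January 2026". The reason given is: "The two-stage split is because schools in Kenya are generally closed from November to January". The layout is: "Each stage of data collection will be done over 2 days in each community, with two enumerators per day".
- **Model.** Under Data analysis: "We will include controls for child age, sex and strata (county) fixed effects". Neither an exposure term nor a stage term is listed.
- **Label.** The same section says: "For the daycare user sample, we will capture the treatment-on-treated effect, but this could be biased if the quality improvement affected the selection of children" (that is, who enrols). Length of exposure is not mentioned as a limit on this estimate.

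**The concern.** A treatment-on-treated label invites the reader to take the estimate as the effect of having received the improved care. Eligibility by enrolment on the day, in a setting with high turnover, does not ensure that a child has received much of it. Some treated children may have been in the improved daycare for a year, others for a few days. Height-for-age accumulates slowly, so a child who joined recently can show almost no effect on it, and probably little on IDELA.

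Such children pull the daycare-user estimate towards zero. Without a start date the analyst can neither describe the exposure that the estimate refers to nor tell a weak programme from a short exposure. The selection caveat in the article concerns which children enrol. It does not cover how long they have been enrolled.

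A second, smaller matter is that data from two stages three months apart enter a regression with no term for stage.

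**Working it through.** **1. The plan's own figure.** The point rests on no stated figure, but the nearest one is the claim under Sample size and power calculations of 80% power for 0.14 SD on anthropometry in each subsample. With a two-sided 5% level (assumed, as the article states none), the minimum detectable effect is (1.96 + 0.84) × √(1/n₁ + 1/n₂) × √DEFF.

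- Baseline sample (1748 and 1597): 2.80 × √(1/1748 + 1/1597) = 0.097 SD before clustering. It reaches 0.14 SD at DEFF = (0.14/0.097)² ≈ 2.08. With 3345/51 = 65.6 children per community, that is an ICC of about (2.08 − 1)/(65.6 − 1) = 0.017.
- Daycare users (330 and 330): 2.80 × √(2/330) = 0.218 SD even at an ICC of 0.

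So 0.14 SD is attainable for the baseline sample but is not reproduced for the daycare users from the article's inputs. Appendix A.2 (not shown) may hold further assumptions. This is a separate matter and no evidence for the present point. It does mean that power figures built on 80% for this sample are conditional.

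**2. Attenuation.** Let p be the share of treatment-arm daycare users, from either stage, whose exposure is too short to have had any effect. Children in control communities have no programme effect at any duration, so only the treatment arm matters here. The expected estimate is (1 − p) × the effect in exposed children. If the stated 80% power is taken as given, power becomes Φ(2.80 × (1 − p) − 1.96). The article gives no value for p, so the values below are assumptions.

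| Assumed p | Share of effect left | 0.14 SD becomes | 0.25 SD becomes | Power, if 80% undiluted |
|---|---|---|---|---|
| 5% | 95% | 0.133 | 0.2375 | 76% |
| 12.5% | 87.5% | 0.1225 | 0.219 | 69% |
| 25% | 75% | 0.105 | 0.1875 | 56% |

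The direction is clear, but the size depends wholly on p.

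**3. Stage term.** The bias from leaving stage out is the stage effect × the difference between arms in the January share.

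- Equal January shares: 0.
- Stage effect 0.1 SD, imbalance 10 points: 0.1 × 0.10 = 0.01 SD.
- Stage effect 0.2 SD, imbalance 10 points: 0.2 × 0.10 = 0.02 SD.

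These inputs are also assumptions. A stage term would not correct short exposure.

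**4. Scope.** The 3345 baseline children come from households identified before randomisation, and their contrast is intention-to-treat. Entry to that sample does not depend on current enrolment, so the attenuation in step 2 does not apply to it.

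**The case against.** The strongest reply is that much of this may be settled elsewhere. Appendix A.1 could hold an entry rule or a roll date, an analysis plan could hold a stage term, and the article already flags turnover and selection as limits on the daycare-user estimate. The first part stands as a possibility. However, the article itself fixes the eligibility definition, the listed controls and the treatment-on-treated label, and as stated these do not fit together.

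Several stronger readings are tempting, and the documents do not support them:

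- **January children have only weeks of exposure after a break from care.** The article says that schools close, not that daycares do. Under Subsample analysis and heterogeneity it distinguishes home and centre care from school-based daycare, so only some providers are clearly tied to schools. A child could have joined an open daycare in November, or joined days before an October visit. The gap is the unrecorded start date, not the January stage.
- **Stage is confounded with arm, or each sample belongs mainly to one stage.** Each stage runs in each community, so stage is crossed with arm by design. Nothing ties either sample to one stage.
- **A definite dilution.** Assuming 25% to 75% of users measured in January, with 20% to 60% of those new and without effect, leaves 1 − 0.25 × 0.20 = 95% down to 1 − 0.75 × 0.60 = 55% of the effect. That range only restates its inputs.
- **January recruitment should be limited to the October roll.** That would select children retained across the gap. If improved daycares retain children differently, it adds selection after randomisation, close to the bias that the article already warns of.

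**Conclusion.** The point holds for the daycare-user sample of 660 children. Their contrast averages over unknown and possibly very short exposure, in both stages, and the treatment-on-treated label does not say so. Recent entrants would move the estimate towards zero. This assumes that the programme effect is beneficial and builds up with time in care. The amount cannot be calculated from the article, and the attenuation and power figures above only illustrate it.

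The intention-to-treat contrast in the 3345 baseline children is not affected. The missing stage term is a minor matter: mainly lost precision, with a bias of about 0.01 to 0.02 SD under a 10-point arm imbalance and an assumed stage effect of 0.1 to 0.2 SD. It is worth correcting because it costs almost nothing.

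**What to change.** 1. Add enrolment start date to the form that daycare parents already return with the date of birth. For children already assessed, ask it afterwards.
2. Report duration of exposure in the daycare-user sample by arm and by stage.
3. Describe the main daycare-user estimate as the effect among current users at their observed exposure, not as an unqualified treatment-on-treated effect.
4. Add a sensitivity analysis by enrolment duration. Read it with caution, because duration may itself be affected by the intervention.
5. Add an October 2025 versus January 2026 indicator to the regressions in the Data analysis section, for precision and as protection if the January share differs by arm.
6. Do not restrict January recruitment to children on the October roll.

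The cost is one form question, one model term, a short table, one sensitivity analysis and a less favourable label for the daycare-user estimate.

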#### Child age data

Our study sample is limited to children born in 2021 or later, and we will use child date of birth to calculate height-for-age z-scores (HAZ) as well as to apply the IDELA, which relies on child age in months. For our first group of children (those in the C-RCT baseline), we have the child’s month and year of birth, as that was recorded in the C-RCT baseline. This information will be verified during our midline survey, when parents are invited to bring their children for the assessment.

For the group of children recruited through their daycare participation, parents will be asked to provide the date of birth of their children in the forms they return to the daycare along with their consent.

#### Sample size and power calculations

As figure 2 shows, we plan to collect anthropometric measurements from 3345 baseline sample children (1748 control and 1597 treatment) and 660 daycare user sample children (330 control and 330 treatment). This yields 80% statistical power to detect a treatment effect of 0.14 SD on anthropometric measurements for each subsample. For child development, we have 80% power to detect a treatment effect of 0.25 SD, reflecting that roughly 60% of children will be in the relevant age range and that the estimated intra-cluster correlation coefficient is likely to be higher. See online supplemental appendix A.2 for more details. These minimum detectable effect sizes are well within the range of measured impacts found from similar interventions (see Dulal *et al,*^22^ development impacts ranging from 0.30 to 0.52 SD; and see Mamun *et al*,^23^ nutrition impacts averaging 0.20 SD).

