**Methods and analysis:**

We combine a cross-sectional observational study of child development and anthropometrics among approximately 4700 children aged 0–5 across 11 counties in Kenya with a cluster randomised controlled trial that measures the impact of improved daycare quality on these outcomes. We use International Development and Early Learning Assessment to measure child development and record child height and weight to measure height-for-age and weight-for-height z-scores. Primary analyses will (1) estimate associations between child development outcomes and nutritional status using multivariable regression models, adjusting for prespecified covariates; and (2) examine differences in outcomes between children attending daycares in communities exposed to quality improvements and children attending daycares in control communities. Subgroup analyses will examine heterogeneity by child sex and daycare participation.

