Evidence from both high-income and low-income settings shows that structured and supportive interactions between caregivers and children are key pathways through which childcare quality influences developmental trajectories.^11^ Providers who are responsive, nurturing and cognitively stimulating promote secure attachment, language development and early learning skills,^12^ while low-quality childcare can constrain children’s socioemotional development and school readiness.^13^ Early childhood nutrition is also fundamental to child development, learning and future academic achievement.^14^ Malnutrition—whether due to insufficient calories, poor dietary diversity or micronutrient deficiencies—can impair brain development, reduce attentiveness and weaken immune function.^1 15^ In informal settlements in Kenya, approximately one-third of residents live below the poverty line, in conditions associated with malnutrition and micronutrient deficiencies.^16^ Roughly half of young children in Nairobi informal settlements are stunted,^17 18^ and we find that 40% of daycares report that at least one child spends the day hungry at least once per week.^10^ Informal daycare attendance may be associated with worse nutrition status,^19^ but this relationship may not be causal if malnutrition is correlated with enrolment decisions. Given this context, it is *a priori* unclear whether attending daycare is positively (or negatively) associated with health outcomes for children in informal settlements.

Although this population is highly vulnerable, data on child development and nutritional status in informal settlements are extremely limited. Families living in these settlements are mobile and hard to reach, making it particularly difficult to collect high-quality data.

We address this gap by (1) documenting child development and nutritional status for approximately 4700 young children in 51 informal settlements across Kenya and (2) assessing the causal impact of improvements in childcare quality on child development and anthropometric measurements for children enrolled in paid daycares within these settlements. A reliable, high-quality measurement of early childhood cognitive and physical development outcomes among a low-income population in Kenya is fundamental for policy design, as is an understanding of the effect of efforts to improve daycare services available to them on these outcomes.

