In this study, we build on an existing cluster randomised controlled trial (C-RCT) that has been underway in informal settlements in Kenya since 2024 and involves nearly 1000 daycare firms.^10^ We will collect and analyse data on child development for children aged 3–5 (roughly 2700 children) and child anthropometric measurements for children aged 0–5 (roughly 4700 children) in the same communities where these daycares operate. The intervention within the C-RCT focuses on improving the quality of paid daycare, including improvements in caregiving practices, infrastructure and the provision of nutritious food. The study sample includes (a) young children from households enrolled in the study before the intervention and (b) young children currently enrolled in centres located in treatment and control communities.

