#### Subsample analysis and heterogeneity

We will examine effects among our two different sample sources: the children recruited through our C-RCT household sample and those recruited from among children currently enrolled in the selected 220 daycares. We will also conduct subgroup analyses along the following dimensions:

Daycare enrolment status: whether using daycare or not; type of daycare used (home and centre vs school-based daycare) and quality of daycare used.Child sex.

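### The planned anthropometry counts add to 4005 children, but the abstract and introduction announce about 4700 for the same children, and the subsample detectable effects need restating once the counts agree

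*Protocol article*

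**What the plan says.** The headline size appears three times. The abstract (Methods and analysis) describes "approximately 4700 children aged 0–5 across 11 counties in Kenya". The introduction (Background and rationale) speaks of "approximately 4700 young children in 51 informal settlements across Kenya", and later in the same section ties that number to the measurement itself: "child anthropometric measurements for children aged 0–5 (roughly 4700 children"). The development assessment (IDELA) is given there as "for children aged 3–5 (roughly 2700 children").

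The operative counts are in Sample size and power calculations, which cites Figure 2 for them: "3345 baseline sample children (1748 control and 1597 treatment") and "660 daycare user sample children (330 control and 330 treatment"). That section says these counts give 80% power for 0.14 SD on anthropometry in each subsample. It puts about 60% of children in the IDELA age range.

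Child recruitment names two sources only: households from the trial's baseline listing, and children enrolled in selected daycares. Data collection says that these two samples are the ones measured. Subsample analysis and heterogeneity describes the second source as children "currently enrolled in the selected 220 daycares".

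**The concern.** The introduction and the sample size section describe the same quantity, namely children aged 0–5 with planned height and weight, and differ by several hundred. The gap is larger than the whole stated daycare-user sample. A reader cannot tell how many children the study intends to measure, or which subsample any missing children belong to.

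This matters because the abstract's second primary analysis compares children in daycares between treatment and control communities, and the daycare-user sample is much the smaller of the two. Its detectable effect depends strongly on its size, and the article assigns it the same 0.14 SD as a baseline sample about five times as large (3345 / 660 = 5.1). A final report measured against the announced 4700 could also appear to fall well short when it had met the stated targets in full.

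**Working it through.** **Totals.** Inputs are from Sample size and power calculations.

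- Baseline: 1748 + 1597 = 3345, as stated.
- Daycare users: 330 + 330 = 660, as stated.
- Sum: 3345 + 660 = 4005.
- Gap to the headline: 4700 − 4005 = 695, and 695 / 4700 = 14.8%.

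Each subsample is consistent within itself; only the total fails. Overlap between the two samples could not close the gap, since children counted in both would lower the number of distinct children below 4005.

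**IDELA.** The stated share is about 60%.

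- 0.60 × 4005 = 2403, which is 297 (11%) below 2700.
- 2700 / 4005 = 67%, whereas 2700 / 4700 = 57%.

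So 2700 sits with 4700, not with 4005.

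**A possible reconciliation.** Reaching 4700 with 3345 baseline children needs 4700 − 3345 = 1355 daycare users, or 1355 / 220 = 6.2 per selected daycare. If 660 were a per-arm count, the total would be 3345 + 1320 = 4665 (six per daycare). As written, 660 / 220 = 3 per daycare. This is inference: neither 1320 nor six per daycare appears in the article.

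**Detectable effects, anthropometry.** Assumptions, because the article does not give these values and refers to appendix A.2: two-sided alpha 0.05, no covariate adjustment, and an intracluster correlation (ICC) shown over a range. With 51 communities and m = N / 51 children per community,

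MDE = (1.960 + 0.842) × √(1/n₀ + 1/n₁) × √(1 + (m − 1) × ICC).

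The plan's own figure first. For the baseline sample (1748 v 1597, m = 65.6), the MDE at ICC 0 is 0.097 SD. The stated 0.14 SD implies a design effect of (0.14 / 0.097)² = 2.08, hence ICC = 1.08 / 64.6 ≈ 0.017. So 0.14 SD can be reproduced for the baseline sample at a modest ICC.

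For the daycare users:

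| Per arm | m | ICC 0 | ICC 0.02 | ICC 0.05 |
|---|---|---|---|---|
| 330 (as stated) | 12.9 | 0.218 | 0.243 | 0.276 |
| 660 (inferred alternative) | 25.9 | 0.154 | 0.189 | 0.231 |

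With 330 per arm at ICC 0, power at 0.14 SD is about 44%, and about 801 per arm would be needed before any clustering. Covariates would have to explain 1 − (0.14 / 0.218)² ≈ 59% of the variance to bring the MDE to 0.14 SD, still at ICC 0. A one-sided test gives 0.194 SD.

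**The case against.** The headline numbers are marked as approximate, they appear only in the abstract and introduction, and no analysis or power statement uses them. The per-arm counts in the sample size section are the operative targets and are internally consistent. Figure 2 and appendix A.2 are not available here and may explain the difference. On this view 4700 is simply an outdated headline.

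Much of this stands. It rules out four stronger readings that a reader might infer.

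- **That the counts behind the power claim are wrong.** The mismatch alone does not show it. If 4700 is the outdated figure, 3345 and 660 may be exactly what was used.
- **That the IDELA total is a second error.** It appears once, it fits 4700, and the 2403 rests on a rounded share of the disputed total.
- **That the daycare-user target is out by a factor of two.** This assumes that 3345 is right and the whole gap lies among daycare users. A low baseline count or an outdated headline fits as well.
- **That field teams will stop short.** Nothing shows field quotas being set from the headline; a team reaching 330 per arm meets the stated plan.

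What does not stand is the appeal to rounding: 4005 rounds to 4000. Nor can the figure be relied on to rescue the text, because the section presents 3345 and 660 as the figure's own numbers. No passage explains 4700 as children approached before losses.

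The detectable-effect point is separate from the totals and would remain if every total agreed. It belongs here only because the correction to the counts must carry through to it.

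**Conclusion.** The contradiction is real: 4005 planned against about 4700 announced for the same measurements, a gap of 695 children or 14.8%, with only two recruitment sources described. The IDELA figure is probably the same discrepancy carried over. The article does not show which count is wrong, and the reading of 660 per arm remains conjecture.

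On either daycare count, the claim of 0.14 SD for both subsamples does not follow under two-sided alpha 0.05 without covariate adjustment: the MDE is at least 0.218 SD with 330 per arm and at least 0.154 SD with 660 per arm, and both rise with clustering. With 330 per arm it already exceeds the 0.20 SD average nutrition impact that the same section cites as a benchmark. This conclusion does not depend on a particular ICC, since it holds at zero. A high covariate R-squared reported in appendix A.2 could change it, but for 330 per arm that would have to be about 59% or more.

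**What to change.** Confirm the target number of baseline children and of daycare users in each arm. Then make the abstract (Methods and analysis), both places in Background and rationale, the sample size section and Figure 2 state the same totals. If the sample size section is right, the headlines become about 4000 children for anthropometry and about 2400 for IDELA. If 4700 is right, correct whichever subsample count is too low.

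Restate the minimum detectable effect separately for the baseline and daycare-user samples from the confirmed counts, giving alpha, ICC and any R-squared assumed, and revise the comparison with published effects to match.

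The cost is a text correction and one rerun of the power calculation. No added recruitment and no change to design or analysis is needed.

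### The 0.14 SD detectable effect claimed for each subsample cannot hold for 660 daycare-user children: 330 per arm gives 0.218 SD at best without covariate gain

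*Protocol article*

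**What the plan says.** All the figures stand in one paragraph of the protocol article, under Sample size and power calculations. The planned anthropometry numbers are "3345 baseline sample children (1748 control and 1597 treatment") and "660 daycare user sample children (330 control and 330 treatment"). The power claim follows directly: "This yields 80% statistical power to detect a treatment effect of 0.14 SD on anthropometric measurements for each subsample".

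The next sentence turns to child development: "For child development, we have 80% power to detect a treatment effect of 0.25 SD". It gives two reasons for the larger figure: "roughly 60% of children will be in the relevant age range", and "the estimated intra-cluster correlation coefficient is likely to be higher". It does not name the sample it refers to. The paragraph then concludes: "These minimum detectable effect sizes are well within the range of measured impacts found from similar interventions". It cites development impacts of 0.30 to 0.52 SD and nutrition impacts averaging 0.20 SD.

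The Data analysis section plans to examine outcomes separately in the two samples, and the Subsample analysis section repeats this. The article does not print the significance level, the ICCs or any covariate R-squared. It refers to supplementary appendix A.2 for details, and their absence from the article is not the complaint here.

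**The concern.** With the same 51 communities, the MDE depends on the number of children, the ICC and the variance that covariates remove. The baseline sample is about five times the size of the daycare-user sample (3345/660 = 5.07). The paragraph nevertheless gives both the same 0.14 SD, and the wording is expressly per subsample, so it cannot be read as a pooled figure.

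The daycare-user sample is the one recruited from the selected daycares. The Data analysis section assigns it the effect on children who actually receive the improved care. Anthropometry is a primary outcome. If the printed figure stands, a null result in daycare users would be set against a claimed sensitivity of 0.14 SD that the sample does not have.

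**Working it through.** **Inputs from the article.** Baseline sample 1748 control and 1597 treatment; daycare users 330 and 330; 51 communities (25 treatment, 26 control); 80% power; about 60% of children eligible for the development assessment; model covariates age, sex and county.

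**Assumptions.** Two-sided alpha 0.05, outcome SD 1, equal cluster sizes m = n/51. R-squared is 0 unless stated. ICC starts at 0, the most favourable non-negative value.

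**Formula.** MDE = (1.960 + 0.8416) × sqrt[(1/n1 + 1/n2) × DE × (1 − R²)], with DE = 1 + (m − 1) × ICC.

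**1. Can the stated 0.14 SD be reproduced in the baseline sample?** Yes.
- ICC 0: 2.8016 × sqrt(1/1748 + 1/1597) = 2.8016 × 0.03462 = 0.097 SD.
- To reach 0.14 SD the design effect must be (0.14/0.097)² ≈ 2.08. With m = 3345/51 = 65.6, ICC = 1.084/64.6 ≈ 0.017.

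So 0.14 SD fits the baseline sample at an ICC of about 0.017. That ICC is back-solved and is not printed in the article.

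**2. Can it be reproduced in the daycare-user sample?** No.
- ICC 0: 2.8016 × sqrt(2/330) = 2.8016 × 0.07785 = **0.218 SD**.
- Power at 0.14 SD, ICC 0: Φ(0.14/0.07785 − 1.960) = Φ(−0.162) = **43.6%**.
- Children needed for 0.14 SD, ICC 0: 2 × (2.8016/0.14)² ≈ 801 per arm, or 1602 in total.
- R-squared needed at ICC 0: 1 − (0.14/0.2181)² = **0.59**.
- ICC needed at R-squared 0: about −0.049, so no non-negative ICC works.
- A one-sided 5% test at ICC 0 still gives 0.194 SD.

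Clustering makes it worse (m = 660/51 = 12.9):

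| ICC (illustrative) | MDE, SD | Power at 0.14 SD |
|---|---|---|
| 0 | 0.218 | 43.6% |
| 0.017 | 0.239 | 37.5% |
| 0.05 | 0.276 | 29.6% |
| 0.10 | 0.323 | 22.8% |

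**3. Could 660 be a misprint?** 3345 + 660 = 4005, whereas the Abstract and the Background and rationale section give about 4700 children. If 660 were per arm (an assumption), the total would be 3345 + 1320 = 4665. The MDE would then be 2.8016 × sqrt(2/660) = **0.154 SD** at ICC 0, with 72% power at 0.14 SD. Reaching 0.14 SD would need R-squared of 1 − (0.14/0.1542)² ≈ 0.18 at ICC 0, and more with any clustering.

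**4. Child development.** Applying the 60% share to daycare users (an assumption, since the article gives it for children overall) leaves 0.60 × 660 = 396, or 198 per arm. At ICC 0 the MDE is 2.8016 × sqrt(2/198) = 0.282 SD, and power at 0.25 SD is 70%. R-squared of about 0.21 would bring this to 0.25 SD at ICC 0; at ICC 0.10 about 0.53 would be needed.

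**The case against.** The strongest defence is that appendix A.2 may hold inputs that explain the figure. For anthropometry this does not work. The covariates named are age, sex and county, and the z-scores are computed on WHO growth standards. An R-squared of 0.59 from those covariates would be extraordinary, and it is the minimum, since it assumes no clustering.

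A second defence is that the sample size, not the MDE, is misprinted. This is plausible. About 4700 children overall and about 2700 aged 3–5 agree better with 660 per arm (4665, and 60% of that is 2799) than with 660 in total (4005 and 2403). It affects how the correction should be made, but 0.14 SD is still missed without covariate gain.

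Three stronger conclusions are tempting, and the article does not support them:

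- **That the 0.25 SD child-development claim is wrong for daycare users.** The per-subsample wording belongs to the anthropometry sentence only. The figure also depends on inputs not shown: R-squared of about 0.21 at ICC 0 would rescue it, and with 660 per arm the MDE is 0.199 SD at ICC 0 and reaches 0.25 SD only at an ICC of about 0.04. What stands is that the sentence leaves its scope open.
- **That the comparison with published effects is false.** The 0.20 SD nutrition benchmark is an average, so an MDE above it is not shown to lie outside the range of measured impacts. For development, 0.282 SD lies below the smallest cited effect of 0.30 SD. What stands is that, at n = 660 without covariate gain, the nutrition MDE exceeds the average cited impact.
- **That 0.239 SD is the correct daycare-user MDE.** It transfers an ICC back-solved from one sample to another recruited differently. It is an illustration; the ICC 0 value is the firm bound.

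**Conclusion.** The anthropometry claim is wrong as written for the daycare-user sample. With 330 per arm the MDE is at least 0.218 SD, more than one and a half times the stated 0.14 SD (0.218/0.14 = 1.56), and power at 0.14 SD is at most about 44%. This rests on a two-sided 5% test, no covariate gain and a non-negative ICC. A one-sided test does not change the conclusion, and only an R-squared of 0.59 or more would.

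The article's figures do not contradict 0.14 SD for the baseline sample. The unclear scope of the 0.25 SD figure and the nutrition comparison need clarification; neither is a demonstrated error. This is an error in a stated power figure for a primary outcome in a sample that will be analysed separately. It does not invalidate the design.

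**What to change.** 1. Reconcile the 660 daycare users (4005 children in all) with the roughly 4700 stated in the Abstract and the Background and rationale section, and say whether 660 is a total or a per-arm number. Do this before recalculating anything.
2. Remove the per-subsample wording. State the anthropometry MDE separately for each sample with its alpha, ICC and R-squared: about 0.14 SD for the baseline sample if the appendix inputs support it, and no better than about 0.22 SD for daycare users if n = 660 and no covariate gain is assumed.
3. Say which sample the 0.25 SD child-development figure refers to. For about 396 daycare users the MDE is about 0.28 SD at ICC 0 without covariate gain, so 0.25 SD should not be implied there unless the stated inputs support it.
4. Qualify the comparison with published impacts by noting that, for nutrition in daycare users, the MDE exceeds the cited average of 0.20 SD.

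These are text changes. No extra enrolment is needed, and the only cost is that the stated figures become less favourable.
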